#### Document review

In addition to qualitative interviews of those in successful AHD partnerships, we will collect formal documents that provide guidance about how successful AHD partnerships are structured. Documents will be requested at the conclusion of the interview and will be shared digitally with the study team. Example documents are Memoranda of Understanding (MOU), which outline the terms of a partnership, project reports from joint research projects, and accreditation documents, which often are required to have information about EBPP implementation and practice-based education (student practica).

#### Qualitative data and document review coding and analysis

Digital recordings will be transcribed verbatim by the Internet-based service Rev (https://www.rev.com/). All transcripts and documents will be analyzed using NVIVO.12 software [59]. A codebook will be developed based on the interview guide, which will be based on EPIS. Each transcript will be coded independently by two team members [60]. The two team members will then review non-overlapping coding in the text blocks and reach agreement on text blocking and coding. Themes from the coded transcripts and documents will be summarized and highlighted with exemplary quotes or in data matrices.

#### Refining strategies to enhance AHD partnership engagement and increase use of EBPPs

A list of AHD partnership features (*e.g.,* characteristics, structures) and processes used to form or maintain AHD partnerships that may contribute to EBPP implementation will be compiled based on emerging themes from the qualitative interviews and document reviews. To create an initial menu of strategies, we will match these features to strategies used in prior work [61–65] or in the Learning Community using a nominal group technique, a structured variation of a small-group discussion, to reach consensus [66]. To refine this list, the investigative team and Practice Advisory Group will review themes to prioritize those that are most likely to be influential for EBPP implementation, as some features may be influential for other outcomes of AHD partnerships such as student practica. We will build consensus as a group using prioritization matrices commonly employed in small group decision making and prioritization activities [67–69]. We will rate partnership features according to characteristics such as appeal, perceived relevance to EBPP implementation, feasibility, cost, and sustainability potential and prioritize based on the combinations of these ratings.

### Experimental Phase: test strategies to improve EBPP implementation through AHD partnerships (positive deviance step 3)

In the experimental phase, we will test strategies to support AHD partnerships and increased use of EBPPs. To test the hypotheses generated in the formative phase, we will conduct a paired, group-randomized study to understand if the strategies used within top engagement AHD partnerships can improve adoption of cancer prevention and control EBPPs among lower engagement AHD partnerships. Fourteen partnerships will be randomized to the implementation arm, which will receive resources and guided facilitation, and 14 will be randomized to a control arm, which will be referred to existing resources in the Learning Community but will not receive new resources or the guided facilitation.

#### Study population and selection of AHD partnerships

Our target audiences for this study are LHD practitioners and academics in lower engagement AHD partnerships as defined by extent of LHD EBPP implementation. We will recruit participants for this study from those identified as the bottom half of the EBPP implementation score created in the formative phase. Randomization will occur after pair matching as in previous community trials, to improve power [70–72]. Matching of partnerships will be based on size of the LHD and how long the AHD partnership has been in existence. Individuals from the LHD and academic institution will be invited to participate in the study. We will recruit 13 LHD staff and academic partners per partnership. LHD staff will include the division or program director for community health promotion or chronic disease prevention (primary contact) along with staff identified by the program director key to supporting cancer prevention and control, *e.g.,* health educators. Academic partners will include professors, research staff, and graduate students from schools or programs of public health, nursing, or other related health disciplines. To increase achievability of the primary outcome, we will limit our sample to LHDs with at least 2 FTEs focused on chronic disease control per our prior research [63]. This provides a total of 364 (28 partnerships X 13 partnership members/partnership) individuals for recruitment into the trial.

#### AHD partnership strengthening strategies

AHD partnerships randomized to receive remote tailored, guided support to improve their partnerships will first participate in a planning period at the beginning of the intervention period to establish the goals for the partnership (Table 3). The study team will facilitate discussions to determine how AHD partnerships want to modify their partnership. We will use the prioritized list of AHD partnership features developed in the formative phase to guide the initial planning period and then assist the partnership members to plan to implement the corresponding strategies focused on their areas of interest. This approach acknowledges that uniformity is unlikely to be effective across partnerships with different needs, capacity, and context [73–76].

**Table 3 Tab3:** Implementation strategy description

	**Strategy: Assess for readiness and identify barriers and facilitators**	**Strategy: Tailored facilitation**
**Actor(s)**	Study staff trained in public health and who have experience working with governmental public health staff	Study staff trained in public health and who have experience working with governmental public health staff
**Action(s)**	Initial videoconference meeting to understand the goals for the partnership, discuss barriers and facilitators, make suggestions, and provide encouragement	Ongoing videoconference calls to reflect on the progress towards goals and the implementation effort, share lessons learned, work through challenges, and discuss any changes that need to be made to goals. Additional implementation strategies (e.g., access new funding, conduct ongoing training) may be recommended for use to match goals
**Target(s) of the action**	Local health department staff and their academic partners	Local health department staff and their academic partners
	Knowledge about and skills to use evidence-based programs and policies, understanding of each partner’s strengths to support implementation	Knowledge about and skills to use evidence-based programs and policies, understanding of each partner’s strengths to support implementation
**Temporality**	The initial meeting will be within the first month of the implementation period	First facilitation meeting should be within one month of initial goal setting meeting
**Dose**	Once for one hour	At least once monthly for up to one hour for the study period (2 years)
**Implementation outcome(s) affected**	Adoption of cancer-related, evidence-based programs and policies	Adoption of cancer-related, evidence-based programs and policies
**Justification**	Local health department practitioners often lack skills to implement evidence-based programs [28, 29]. Understanding context-specific barriers and facilitators to utilizing evidence-based practices is key to supporting change within local health departments [14, 32–34, 82].	Tailoring is essential because uniformity is unlikely to be effective across partnerships with different needs, capacity, and context [73–76].

Description categories taken from Proctor et al. 2013 [83]

Once the initial planning period is complete, the research team will be knowledge brokers to provide facilitation and improve AHD partnership engagement in ways that match the goals set by the partnership. Based on our prior work, we anticipate LHD staff will need guided facilitation and training focused on: 1) assistance with strategic planning processes for implementing a strategy of interest; 2) consultation on overcoming barriers to implementing EBPPs; 3) help identifying funding sources and grant writing to fund joint research projects; and 4) identification of online training sources to support evidence-based decision making and strengthen partnerships. Instead of providing these supports directly to LHD staff as in previous work, we will work with the AHD partnership to meet these needs. We will regularly assess AHD partnerships’ progress towards goals, and adjust goals and strategies based on the progress.

#### Quantitative measures

To understand the effects of AHD partnership strengthening activities, we will measure the adoption of cancer-related EBPPs (primary outcome) and other partnering, individual- and organizational-level covariates. Data will be collected at baseline (prior to randomization) and at the end of the study.

#### AHD partnership engagement

Measures will include the same collected in the formative phase, including the adoption (use) of cancer prevention and control EBPPs (primary outcome); AHD partnering activities; organizational supports for evidence-based decision making [77]; joint research projects; publishable practice-based research; shared staff; and shared financial resources.

#### Implementation costs

Given the importance of cost in public health decision making and for future scale up and replication studies [78–80, 84, 85], costs associated with various strategies will be collected using a pragmatic approach proposed by Cidav and colleagues [86]. The approach blends time-driven activity-based costing, a process-based micro-costing method used in business accounting, with Proctor’s framework for reporting implementation strategies [86]. Costs are tracked in a step-wise manner: 1) name each implementation strategy and list the associated actions, actors, and temporality; 2) determine the frequency and average duration of each implementation action by actors and actors’ total time spent on each action; 3) determine the price per hour of each actor; 4) determine non-personnel, fixed resources and their expenses; and 5) calculate total costs. This approach will allow us to describe the relationship between costs and outcomes, both cumulatively and by implementation action. Costs associated with research activities will be separated from other implementation costs.

#### Organizational covariates

Information about the AHD partnership will be collected, including the year the partnership was established, the number of individuals involved in the partnership, and bridging factor dimensions of the partnership (*e.g.,* partnership resources and structures to support EBPP implementation). Characteristics of the LHD (FTEs, annual expenditures, jurisdiction size, Public Health Accreditation Board accreditation status) and academic institutions (2- or 4-year institutions, Public Health Schools or Programs) will be collected.

#### Individual covariates

LHD staff and academicians’ age group, years in current position, job title, and academic degrees will be collected. Previously validated surveys will assess LHD staff’s evidence-based decision making skills [61, 87, 88].

#### Qualitative measures

Participants in partnerships randomized to the active implementation arm will be invited to participate in a post-study interview to understand how and why changes did or did not occur, according to EPIS framework constructs that may explain the quantitative findings in the study. Similar to the formative phase, interview questions will assess how partnerships were structured and what processes and resources AHD partnership members thought were most and least impactful for enhancing the adoption of EBPPs.

#### Process evaluation

Process evaluation data will assist us in determining the use and reach of our strategies and to assess whether outside events impacted our findings. Examples of process measures include requests for technical assistance, participation and satisfaction with capacity building initiatives, inclusion of a greater focus on EBPH and EBPPs in agency plans, becoming an accredited or reaccredited health department, and external funding granted to an LHD for cancer control-related programming.

#### Power calculation

This study uses a paired, group randomized design. By using tight matching criteria, we will balance potential confounding factors (*e.g.*, FTEs, county size, duration of partnership) that may affect EBPP implementation. As a result, the between-cluster variation will be reduced, and statistical power increases [89, 90]. Based on our preliminary studies and values of intraclass correlation coefficients (ICC) in the literature [30, 62, 91–96], we estimated a range of effect sizes and ICCs. We calculated a median ICC from similar studies and developed a range based on a 50% decrease and increase around the median (range 0.009 to 0.027). We are interested in the changes in AHD partnership characteristics and adoption of EBPPs from baseline between the intervention and control arms. Drawing from previous work [63, 92, 93], we hypothesize that the scores in the intervention arm will be between 10 and 20% higher than the control arm for implementation of EBPPs. Following Donner [97] and Thompson [98], and using the most conservative estimates of effect sizes and ICCs, we estimate the number of clusters needed is 28 AHD partnerships (*n = *14 per arm) and the number of subjects is 13 at baseline (total = 364) to ensure 9 at two years post-randomization (total = 252), given a power of > 90% and an overall Type I error of 5%. This assumes about a 70% retention rate of subjects and allows for attrition of one cluster.

### Quantitative analyses

We will follow Donner [97] for analysis of matched-pair quantitative data. We consider the difference in the mean change between intervention and control EBPP implementation scores in an AHD partnership pair as the unit of analysis and will use the weighted paired t-test (with the cluster size as weights) if the cluster size varies across pairs. We will use the permutation test in which we compare the observed difference with the null distribution derived from the permutation procedure. For cluster-level adjusted analyses, we will follow Thompson’s approach [98] to obtain the adjusted mean first for each individual and for each partnership, then the adjusted difference in mean change in a pair. Modeling details are available upon request.

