#### Measures

The survey is designed to assess engagement related to implementation of cancer prevention and control EBPPs (Table 1) [11, 52]. Adoption of EBPPs will be the variable used to characterize positive and negative deviants and is the primary outcome for the trial. Respondents are presented with a list of evidence-based programs and policies taken from the *Community Guide*, reflecting the program areas in which respondents work. EBPPs are focused on primary or secondary prevention of cancer, grouped into categories used in the *Community Guide*: healthy weight management, physical activity promotion, healthy eating promotion, tobacco use prevention and/or cessation, HPV vaccination, cancer screening, health equity/social determinants of health, maternal and child health, and environmental health [11]. EBPPs that are recommended with sufficient or strong evidence from the Preventive Services Task Force Review are included in the survey. Respondents indicate whether they currently implement (i.e., have adopted) a given EBPP, and a summary variable will be created to reflect adopted EBPPs. This item has been used in our previous work and has demonstrated sufficient test–retest reliability [63]. We will also assess well-recognized outputs and outcomes of successful, productive AHD partnerships [41]. Quantitative indicators include: AHD partnership structures and activities; AHD partnership strengths; organizational supports for evidence-based practice; delivery of evidence-based interventions to address chronic diseases; individual public health skills regarding evidence-based public health; leadership and organizational characteristics; and sustainability of public health programs.

**Table 1 Tab1:** Survey measures

Survey section	Number of items	Type of variables	Sample items	Item sources
Screening questions	2	Check one, yes/no/unsure, check all	Primary organization, participation in an AHD partnership	New
Academic-Health Department Partnerships	16	Check all, Likert 5-point scale, yes/no,	Characteristics of AHD partnership, training topics addressed by partnership, practice-based research	New, Public Health Workforce Interests and Needs Survey, Brewster 2019, Chen 2008
Interventions to address chronic diseases	23	Check all, yes/no/unsure, open response	Delivery of evidence-based interventions by organization and by AHD partnership	New, Erwin 2019, the Community Guide

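### The primary analysis subtracts the baseline EBPP score instead of adjusting for it; the test is valid, but with 14 pairs it may give up some power

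*Protocol article*

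**What the plan says.** Under Quantitative analyses, the primary quantity is "the difference in the mean change between intervention and control EBPP implementation scores in an AHD partnership pair as the unit of analysis". The authors "will use the weighted paired t-test (with the cluster size as weights) if the cluster size varies across pairs", and they also plan a permutation test. A cluster-level adjusted analysis follows; it too ends in mean change ("then the adjusted difference in mean change in a pair"), and its covariates are not named there.

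On timing, Quantitative measures states: "Data will be collected at baseline (prior to randomization) and at the end of the study". On pairing, Study population and selection of AHD partnerships states: "Matching of partnerships will be based on size of the LHD and how long the AHD partnership has been in existence". The Power calculation section gives FTEs, county size and partnership duration as examples of what matching balances. The adoption score is in neither list, nor is it among the organizational and individual covariates.

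The trial sample is drawn from "those identified as the bottom half of the EBPP implementation score created in the formative phase". That measure is also the outcome: "Adoption of EBPPs will be the variable used to characterize positive and negative deviants and is the primary outcome for the trial".

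**The concern.** After randomization, both a change score and a baseline-adjusted follow-up score estimate the treatment effect without bias. They differ in how they use baseline. The change score assumes that one unit of baseline difference carries forward as exactly one unit at follow-up. Adjustment estimates that slope from the data.

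When the true slope is well below 1, subtraction over-corrects chance baseline differences within a pair and adds noise. Because pairs are not matched on the score, such differences will occur. With 14 pairs there is little averaging to absorb them. What is at stake is the power of the primary comparison, not its type I error.

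**Working it through.** **The plan's own figures.** The counts agree: 28 × 13 = 364, 28 × 9 = 252, and 9/13 = 69%, close to the stated 70% retention. The stated power above 90% cannot be reproduced, because no standard deviation is given for the score or its change. It is therefore used below as an anchor and not disputed.

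**Inputs.** 14 pairs and 5% type I error (Power calculation; two-sided assumed, as sidedness is not stated). The correlation r, between baseline and follow-up within-pair differences in mean score, is not given. It is an assumption here, run from 0.3 to 0.9 with equal variances at the two times.

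**Formulas**, per unit of score variance:
- Change score: 2(1 − r)
- Follow-up score alone: 1
- Baseline-adjusted: 1 − r²
- Change over adjusted: 2(1 − r)/(1 − r²) = 2/(1 + r)

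At r = 0.3, change gives 2 × 0.7 = 1.40 and adjusted gives 1 − 0.09 = 0.91, a ratio of 1.54. Below r = 0.5 the change score is noisier than ignoring baseline altogether, since 2(1 − r) exceeds 1.

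**Power, including the cost of the slope.** I simulated 14 pair differences with the effect set so that the paired t-test on change (13 df) has 90% power. Adjustment is the intercept from regressing follow-up difference on baseline difference (12 df).

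| r | Change ÷ adjusted variance, 2/(1+r) | Power, change | Power, adjusted |
|---|---|---|---|
| 0.3 | 1.54 | 90% | about 97% |
| 0.5 | 1.33 | 90% | about 94% |
| 0.7 | 1.18 | 90% | 91–92% |
| 0.8 | 1.11 | 90% | about 90% |
| 0.9 | 1.05 | 90% | 88–89% |

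Type I error was about 5% for both tests. The slope is not free: the realized variance reduction is about 29%, 18%, 7% and 2% at r = 0.3, 0.5, 0.7 and 0.8, and at 0.9 the variance rises by 3 to 4%.

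**If true power is higher.** Suppose the 90% refers to a 10% effect. By noncentral t with 13 df, change scores then have about 98% power at a 12.5% effect and 99.8% at 15%. At 12.5% the gain from adjustment is about 1.5 points at r = 0.3 and 0.3 points at r = 0.7. At 15% it is negligible.

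**Effect of selection on r.** Assume the formative survey, trial baseline and follow-up scores share a common correlation ρ. Keeping the bottom half on the first leaves 1 − 2/π = 0.363 of its variance, so r among those selected is (ρ − 0.637ρ²)/(1 − 0.637ρ²). This takes 0.5 to 0.41, 0.7 to 0.56, 0.8 to 0.66 and 0.9 to 0.79. Simulated power in the selected sample, change against adjusted, was 90% v 96%, 90% v 93%, 90% v 92% and 90% v 90%.

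**The case against.** The strongest reply is that nothing here is invalid. The change-score contrast is unbiased, follows a cited matched-pair method and fits the stated interest in change from baseline. All of that stands, and it limits the point to efficiency. It does not remove the point: under randomization both analyses estimate the same effect, and the Aim 2 hypothesis is a between-arm comparison at two years.

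Second, the size rests on a correlation the documents do not supply, and r could be high. The score records what an organization currently implements, has reported test–retest reliability, and is averaged over about 9 to 13 respondents. This also stands: near r = 0.9 adjustment costs 1 to 2 power points.

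Third, the article offers modeling details on request, so the adjusted analysis might include the baseline score. That can be neither confirmed nor excluded, but the unadjusted primary test is as stated.

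A reader might also infer that recruiting low scorers makes a low r certain through regression to the mean. The documents do not support this:
- Selection is on the formative survey (late 2023 to early 2024), not on the trial's own baseline (second half of 2024), so range restriction is indirect and milder.
- Regression to the mean results from imperfect correlation and does not cause it. It affects both arms alike.
- Staff turnover is no firm argument either. The plan describes retention of recruited members, so leavers reduce numbers and do not necessarily reduce r.

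**Conclusion.** The point holds as a matter of efficiency. The plan fixes the baseline coefficient at 1 although a pre-randomization score is available and unmatched. If change scores have 90% power with 14 pairs, the expected gain from adjustment is about 7 points at r = 0.3, 4 at 0.5, 1 to 2 at 0.7 and none near 0.8, with a loss of 1 to 2 points near 0.9. Selection on the earlier survey may move r toward the range where adjustment helps, but the documents do not establish by how much.

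The size assumes roughly normal pair differences, equal variances at the two times, equal weights and all 14 pairs complete. It shrinks if true power is well above 90%. A reader might infer bias, or that the claimed power is wrong; neither follows. The test keeps its 5% level, and the power claim cannot be checked without a standard deviation.

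**What to change.** Before any follow-up data are analyzed, restate the primary test as follows.

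- For each pair, compute the intervention-minus-control difference in mean follow-up score and the same difference in mean baseline score.
- Regress the first on the second, keeping the planned cluster-size weights, and take the intercept as the treatment effect.
- Test it by within-pair permutation: swap the arm labels within pairs, which reverses the sign of both differences, and refit each time. Alternatively use t with (complete pairs − 2) degrees of freedom. That is 12 with all 14 pairs, or 11 if the loss of one cluster breaks a pair.
- Keep the planned mean-change analysis as a sensitivity analysis.
- If the authors hold earlier data on this measure, state the baseline–follow-up correlation they expect, so the choice rests on a figure.

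The cost is a change of wording and one degree of freedom, with no new data, sites or visits. The downside is no gain near r = 0.8 and a loss of about 1 to 2 power points near 0.9.
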